### Feasibility economic evaluation

In the future definitive study, an economic evaluation of the intervention will be conducted from an National Health Service and personal and social services perspective, with results expressed in terms of incremental costs, quality adjusted life years (QALYS) and net monetary benefits and will likely include a lifetime horizon. However, the focus for our economic feasibility study is on optimising the quality of data collected for the first 90 days post randomisation. This is particularly challenging because patients may be stepped down from ICU to different wards, and reporting needs to effectively track the patient’s recovery through a complex system.

The focus for the feasibility study will be on collecting detailed resource use data on the components of this multicomponent intervention (eg, physiotherapist and dietitian staff time; use of rehabilitation aids and dietary interventions) and resources relevant in the broader healthcare system 90 days following randomisation. Details relating to the intervention will primarily be captured by case report forms completed prospectively. Subsequent healthcare resource use (including primary care) related to the patients care (which is not covered by the case report forms CRFs) will be captured via a validated resource use questionnaire (Modular Resource Use Measure), supplemented by some resource use items relevant to the personal social services perspective.

### Sample size

Since this is a feasibility study, the sample size is not determined by a power calculation but rather aims to estimate the rate of recruitment and retention to inform the future trial. We aim to recruit a total of 60 patients, with an equal number (maximum of n=30) from each site and equal random allocation to control and intervention groups. The sample size enables a high probability of continuing to a definitive RCT. For example, for retention rate, progression to definitive RCT will be considered if the estimate is ≥40%. The probabilities of getting a retention estimate ≥40% in each group when the true rates are 50% (low rate) and 80% (a good rate in definitive RCTs) are 0.82 and 1, respectively, which are high. We estimate that we will have sufficient data to identify key issues and themes after having interviewed approximately five members of staff and eight patients from each site unless saturation is deemed to be achieved before this point.

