### Data analysis

Results will be reported in accordance with the Consolidated Standards of Reporting Trials extension to randomised pilot and feasibility trials^30^ and the Consolidated Criteria for Reporting Qualitative Research.^31^

For each of recruitment, retention and outcome measure completion data, rate (as a percentage) and corresponding 95% CI will be computed. Outcomes data (including health economic data) will be analysed descriptively by an appropriate member of the research team using means, range and measures of variance (CIs, SD) for continuous variables, and count (n) and percentages (%) for categorical variables. Distribution of DAOH-30 and DAOH-90 data will be explored to determine the best model to use to analyse them (eg, whether t-test or a model for count data) and to plan a definitive RCT.

Intervention fidelity will be assumed if 70% of planned sessions are completed from those available and broken down by facilitator to examine variation between provider sites. During fidelity scoring, examples of good practice will be identified for training during the main trial. A traffic light system shown in table 2 that is recommended for best practice will be used as a guide for progression to a definitive trial.^32^

**Table 2 T2:** ‘Traffic light’ system to determine progression to a definitive trial

	Green(trial feasible)	Amber(may be feasible with modification)	Red(likely unfeasible)
Recruitment of proposed rate (%)	100%(60 participants)	99%(36–59 participants)	<60%(<36 participants)
Retention rates—defined as collection of primary outcome measure (days alive and out of hospital)	100%(60 participants)	60–99%(36–59 participants)	<50%(<36 participants)
Intervention fidelity (physiotherapy)Proportion of available sessions completed	> 70%	40–70%	<40%
Intervention fidelity (nutrition)Proportion of prescribed supplements taken	>70%	40–70%	< 40%

Verbatim anonymised transcripts of semistructured interviews will be thematically analysed.^33^ Codes and themes will be identified from the data and refined using an iterative process. Analysis of interview transcripts will be supported by NVivo V.12 (NVivo qualitative analysis software; QSR International V.12).

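### Retention has a 40% progression level in the sample-size section but a 60% (or 50%) level in Table 2, and the stated 0.82 chance of continuing belongs only to the 40% level

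*Protocol article*

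**What the plan says.** The Sample size section of the protocol article plans for 60 patients ("We aim to recruit a total of 60 patients") with "equal random allocation to control and intervention groups", so 30 per group. It asserts that "The sample size enables a high probability of continuing to a definitive RCT" and illustrates this with retention: "progression to definitive RCT will be considered if the estimate is ≥40" per cent. It then gives the operating characteristic, group by group: the chances of reaching that level "when the true rates are 50% (low rate) and 80% (a good rate in definitive RCTs) are 0.82 and 1, respectively". It remarks that both values are high.

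Table 2 in the Data analysis section is named as the guide for moving to a definitive trial. Its retention row, defined by collection of days alive and out of hospital, has three bands:

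- green: 100% (60 participants);
- amber: "60–99%(36–59 participants");
- red, the band for a trial that is probably not feasible: "<50%(<36 participants").

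The recruitment row of the same table pairs the count of fewer than 36 with less than 60%.

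**The concern.** Retention is one of the primary feasibility outcomes, and the abstract says that these determine whether a definitive trial is feasible. A progression criterion should give one verdict for each possible result. Here the lower limit is 40% in one section and 60% by count in another, with 50% printed as the percentage in the red cell. For a range of results the two sections give opposite messages, and for part of that range Table 2 does not agree with itself. The one numerical argument offered for 60 patients is also worked out for a cut-off that the progression table does not use. If retention turned out poor, the team would have to decide after seeing the data which number governs.

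**Working it through.** **Inputs.** Total 60, 30 per group, cut-off 40%, true rates 50% and 80% (all Sample size). Table 2 lower limits: 36/60 = 60% by count; 50%, i.e. 30/60, by the percentage in the red cell. X is the number retained, binomial with the stated n and true rate p. Probabilities are exact tails, P(X ≥ r) = Σ C(n,k) p^k (1−p)^(n−k) for k = r to n. Joint figures assume independent groups with the same true rate.

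**1. The plan's own figure.** 40% of 30 is 12.

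| Reading, n = 30 per group | p = 0.5 | p = 0.8 |
|---|---|---|
| One group, X ≥ 12 | 0.900 | ≈1 |
| One group, X > 12 | 0.819 | ≈1 |
| Both groups, X ≥ 12 in each | 0.900² = 0.810 | ≈1 |

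The stated 0.82 matches a strict inequality in one group (0.819) and is close to both groups passing (0.810). The literal one-group reading of at least 40% gives 0.90. On any of these readings the figure belongs to a 40% cut-off.

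**2. The same scenarios under Table 2 (all 60 participants).**

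| Not red if | p = 0.5 | p = 0.6 | p = 0.8 |
|---|---|---|---|
| X ≥ 36 (count) | 0.078 | 0.556 | 0.9999 |
| X ≥ 30 (percentage in red cell) | 0.551 | 0.956 | ≈1 |

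Applying 60% per group (at least 18 of 30) does not restore the 0.82: at p = 0.5 it gives 0.181 for one group and 0.181² = 0.033 for both.

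**3. Results on which the texts disagree.**

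| Retained of 60, with ≥12/30 in each group | Sample size section | Table 2 by percentage | Table 2 by count |
|---|---|---|---|
| 24–29 (40% to 48%) | progression considered | red | red |
| 30–35 (50% to 58%) | progression considered | no band | red |
| 36–59 (60% to 98%) | progression considered | amber | amber |

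**4. How likely a contradictory result is.** Summing the product of the two group distributions over all pairs with at least 12 in each group and a total below 36:

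| True retention | P(≥40% in both groups, yet red by count) |
|---|---|
| 50% | 0.73 |
| 60% | 0.43 |
| 70% | 0.04 |
| 80% | 0.0001 |

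**The case against.** The language is soft. The 40% figure is introduced as an example, progression is only to be considered at that level, Table 2 is a guide, and red is not an automatic stop. The sample size is expressly not based on a power calculation. This lowers the stakes but does not reconcile the numbers: the same retention cannot sensibly be both the level at which progression is considered and the level marked as probably not feasible.

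The two sections also use different bases, per group and overall. The conflict survives this, since 12/30 in each group is 24/60, which is red by both figures.

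The 50% in the red cell is probably a slip. The amber band, the red count and the recruitment row all indicate 60%, so the substantive conflict is 40% against 60%.

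Two stronger readings are not supported. A reader might infer that the claimed high chance of continuing fails altogether. It does not: at true retention of 80% the chance of avoiding red is 0.9999, provided amber counts as continuing. A reader might also infer that a contradictory result is to be expected. That is so only near 50%, which the protocol itself calls a low rate and does not say it expects. Because death within 30 days is scored as 0 on days alive and out of hospital, a death need not make that outcome missing.

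**Conclusion.** The contradiction stands, and nothing elsewhere in the article resolves it. Progression on retention is considered at 40% per group in one section, while the progression table calls anything below 36 of 60 red and misstates that limit as 50%.

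In the protocol's 50% scenario the stated 0.82 becomes 0.08 under the table's count, or 0.55 under its printed percentage. With probability 0.73 the result would pass the 40% rule in both groups and still be red by count. In the 80% scenario the assurance holds.

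These figures rest on the full 60 being recruited, 30 per group, binomial retention with a common true rate, and amber being treated as continuing. If green were required, meaning all 60 retained, the chance would be close to zero in both scenarios (about 1.5 × 10⁻⁶ at 80%). Because this is a decision threshold for a primary feasibility outcome, it should be corrected before the results are known. It does not affect any estimate of treatment effect.

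**What to change.** Use one retention cut-off in both sections and say whether it applies to each group or to all 60.

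**If 60% is meant**, as the rest of Table 2 suggests:

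- change the red percentage for retention from 50% to 60%, so that it agrees with 36/60;
- replace 40% in the Sample size section with at least 60% (36/60);
- restate the probabilities of avoiding red on the pooled basis: 0.08, 0.56 and above 0.999 at true retention of 50%, 60% and 80%;
- limit the sentence on the high probability of continuing, and the closing remark that the probabilities are high, to the 80% scenario. Otherwise they would stand beside a stated 0.08.

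**If 40% is meant**, change the retention row of Table 2 to match (red below 40%, fewer than 24 of 60; amber from there) and state which rule gives 0.82, since at least 12/30 gives 0.90 in one group and 0.81 in both.

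Either way the change is to one paragraph and one table row, with no change to sample size or data collection. The cost of the 60% option is a less favourable stated probability at 50% retention.

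### The printed probability of 0.82 does not belong to the ≥40% retention rule (0.90 per group, 0.81 for both groups), and the 40% threshold contradicts Table 2

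*Protocol article*

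**What the plan says.** The Sample size section of the protocol article plans as follows: "We aim to recruit a total of 60 patients, with an equal number (maximum of n=30) from each site", with "equal random allocation to control and intervention groups". It claims that "The sample size enables a high probability of continuing to a definitive RCT" and illustrates this with retention, where "progression to definitive RCT will be considered if the estimate is ≥40"%. The figures follow in one sentence. It opens "The probabilities of getting a retention estimate ≥40% in each group when the true rates are 50% (low rate") and ends "80% (a good rate in definitive RCTs) are 0.82 and 1, respectively, which are high".

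Table 2, in the Data analysis section, sets the traffic-light criteria for the same quantity, defined there as collection of days alive and out of hospital. Green is 100% (60 participants). Amber reads "60–99%(36–59 participants"). The red cell pairs a percentage below 50 with a count below 36. No retention cell mentions 40%.

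**The concern.** The section gives every input needed to recompute its probability, and the result for the rule as written is not 0.82. This is the only quantitative support offered for the choice of 60, apart from the interview numbers, so it should match the rule that it illustrates.

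The threshold is the larger issue. Retention is a primary outcome and a progression criterion, yet the article gives two incompatible boundaries for it. A retention estimate between 40% and 49% would allow progression to be considered under the Sample size section, but would be red, meaning likely unfeasible, in Table 2. Whoever takes the progression decision could cite either place. The probabilities printed in support of the sample size apply to only one of them.

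**Working it through.** **Inputs, all from the Sample size section unless noted**
- Total 60 with equal allocation, so n = 30 per group.
- Rule: estimate ≥40%. Since 0.40 × 30 = 12 exactly, the rule is X ≥ 12, where X is the number retained in a group.
- True rates: p = 0.5 and p = 0.8.
- Printed probabilities: 0.82 and 1.
- Table 2: the amber/red boundary by count is 36 of 60; the percentage printed in the red cell is 50%, which is 30 of 60.

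**Formula.** X ~ Binomial(n, p), and P(X ≥ r) is the sum over k = r, …, n of C(n,k) p^k (1−p)^(n−k).

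**Reproducing the printed figures**
- Strictly more than 40%, p = 0.5: P(X ≥ 13) = 0.8192, which rounds to the printed 0.82.
- At p = 0.8: P(X ≥ 13) and P(X ≥ 12) are both above 0.99999, so the printed 1 reproduces either way.

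**The rule as written, p = 0.5**
- The two versions differ by P(X = 12) = C(30,12)/2^30 = 86,493,225/1,073,741,824 = 0.0806.
- Per group: P(X ≥ 12) = 0.8192 + 0.0806 = 0.8998, or 0.90.
- Both groups, taken as independent with the same true rate: 0.8998² = 0.8096, or 0.81.

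**Other routes to 0.82 under the ≥ rule, p = 0.5**
- Normal approximation without continuity correction: 0.863.
- Normal approximation with continuity correction: 0.899.
- Both groups pooled, P(X ≥ 24 of 60): 0.954.

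None of these gives 0.82.

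**Against Table 2**
- 40% of 60 is 24. That is below 50% and below 36, so it is red on either entry in the cell.
- 36/60 = 60%, so the two entries in the red cell describe different boundaries. Counts from 30 to 35 (50% to 58%) are red by count, but by percentage they fall in neither red nor amber.

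**Probability of avoiding red, n = 60 pooled**

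| Boundary | True 50% | True 80% |
|---|---|---|
| ≥36 of 60 (count in the red cell) | 0.078 | 0.9999 |
| ≥30 of 60 (percentage in the red cell) | 0.551 | 1.00 |

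These are pooled figures, because Table 2 counts participants out of 60. They are not on the same footing as the per-group 0.90.

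**The case against.** **The figure is nearly right on one reading.** The phrase in each group can mean both groups together, and that gives 0.81, about one point from 0.82. This stands in part: it makes it too categorical to call 0.90 the only correct value. But 0.8096 does not round to 0.82, whereas the off-by-one version does, and the section writes ≥ for the rule and again for the probability.

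**The number is illustrative.** The section says that the sample size is not set by a power calculation, introduces retention as an example, and says only that progression will be considered. On the per-group reading the slip is conservative, since 0.82 understates 0.90. On any of these readings the probability remains high in the section's own terms. All of this stands and limits the severity.

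**A stronger reading is tempting.** The section calls 50% a low rate and then counts a high chance of passing there as a merit. A reader might infer that the reasoning is backwards and that 0.82 or 0.90 is really the risk of wrongly progressing. The ≥40% rule does not support this. A true rate of 50% lies above the threshold, so passing there is the decision that the rule intends, and 50% can be read as a pessimistic but acceptable case. Wrong progression under this rule concerns true rates below 40%, where the per-group chance of passing is 0.35 at a true rate of 35%, 0.16 at 30% and 0.01 at 20%. It is fair to say that a 40% rule separates 50% from 80% weakly (0.90 against 1.00), but that is a comment on the choice of threshold.

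**Table 2 read by count alone.** A reader might also take 0.08 as the one true chance of passing at 50% under Table 2. That uses the count and ignores the percentage in the same cell, which gives 0.55. Until the cell is corrected, only the range from 0.08 to 0.55 can be stated.

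**Conclusion.** The point holds in two parts.

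1. The printed 0.82 is wrong for the stated ≥40% rule on either reading of in each group. The correct value is 0.90 per group (8 points higher) or 0.81 jointly (1 point lower). The likeliest explanation, though the article cannot confirm it, is that strictly more than 40% was computed. The figure of 1 at a true rate of 80% is right.
2. The 40% retention threshold contradicts Table 2, where 40% is red, and Table 2's red cell is internally inconsistent. This matters more, because it bears on the progression decision itself.

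The severity is minor to moderate, since neither part changes the 60 patients, the allocation or the analysis. The figures assume exactly 30 analysed per group, independent participants, a common true rate in both groups for the joint and pooled values, and exact binomial probabilities.

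**What to change.** - In the Sample size section, say whether the probability is per group or for both groups, and print 0.90 or 0.81 to match the ≥40% rule. If strictly more than 40% was intended, change the sign in both places and keep 0.82 as a per-group figure.
- Reconcile the retention threshold between the Sample size section and Table 2, and make the percentage and count in the red cell agree, leaving no gap below amber.
- Recompute the probabilities for the agreed boundary. At true rates of 50% and 80% they are about 0.08 and >0.99 for at least 36 of 60, or 0.55 and 1.00 for at least 30 of 60. State whether the boundary applies per group or to all 60.
- Describe the probability of passing at a true 50% as a risk of wrongly progressing only if the agreed boundary lies above 50%. While the ≥40% rule is kept, that label would be an error.

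The cost is a sentence or two in the Sample size section and one row of Table 2. Nothing changes in the design, recruitment target or data collection. The boundary should be settled before the retention results are seen.

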### Assignment of interventions

#### Randomisation

Participants will be randomised in a 1:1 ratio to either the intervention or standard care group using an electronic randomisation system, which will facilitate allocation concealment. Randomisation will be stratified by study site.

#### Blinding

Given the nature of the intervention, it is not possible to fully blind physiotherapists, dietitians or participants to group allocation. However, all assessments will be completed by a team member blinded to randomisation and group allocation. This will reduce the chance of bias throughout the assessment process.

### Data collection, management and analysis

#### Data collection

Clinical data are collected at baseline (pre randomisation), daily for up to 14 days post-ICU discharge or hospital discharge (whichever comes sooner) and at 30 and 90 days post randomisation. Data collected are outlined in the study schematic in figure 2 and detailed in table 1.

**Figure 2 F2:**
[figure not shown]
Consolidated Standards of Reporting Trials pilot and feasibility trials flow schematic. PHOENIX, Physiotherapy and Optimised Enteral Nutrition In the post-acute phase of critical illness.

**Table 1 T1:** Timing of visits and data collection

Baseline (pre randomisation)	Confirmation with inclusion and exclusion criteriaDate and time of consentPatient demographics (age, sex, ethnicity, height, weight)Relevant clinical history (depression, anxiety, comorbidities)Primary admission diagnosisICU length of stayDuration of sedationDuration of mechanical ventilationMMSWeightHospital Malnutrition Score (GLIM criteria)Barthel IndexHand grip strengthMid-arm circumference/triceps skin fold30 s sit to stand
Daily for 14 days or until hospital discharge	Frequency and level of mobilisation (MMS)Nutrition and calories consumedTherapy contacts and durationMobilisation-related complications
End of intervention/hospital discharge	WeightBarthel indexEQ-5D-5LHand grip strength30 s sit to standPost-ICU length of staySemistructured interviewsMortality
30 days post randomisation	WeightEQ-5D-5LGrip strengthMid-arm circumference/triceps skin fold30 s sit to standMortalityResource use (MODRUM)Return to work or normal activity
90 days post randomisation	MortalityResource use (MODRUM)Return to work or normal activity

EQ5D-5L5 level EQ5D versionGLIMGlobal leadership initiative on malnutritionICUintensive care unitMMSManchester Mobility ScoreMODRUMModular Resource Use Measure

In addition to the primary outcome of DAOH, we propose to collect several secondary measures at 30 days and 90 days for evaluation. To enable this, where possible the 30-day and 90-day assessments will be completed face to face in a hospital clinic, if the participants have an appointment scheduled. If this is not possible due to the participant being out of area, unable to travel to the hospital or an appointment is not scheduled, components of the assessment identified will be completed via telephone or video conferencing (outlined in table 1).

### Data management

All data for an individual participant will be extracted from patient charts by the principal investigator or their delegated nominees and recorded in the CRF, either on paper or on the online, validated and GCP compliant electronic data capture (EDC) system. Participant identification in the CRF will be through their unique participant study number allocated at the time of randomisation. Data will be collected from the time the patient is considered for entry into the trial through to their discharge from hospital. If a participant were to pass away or withdraw during the study, identifiable data already collected with consent would be retained and used in the study. A withdrawal form will be completed, and no further data would be collected, or any other research procedures carried out on or in relation to the participant.

Data from the CRF will be entered and stored on the EDC system, as described above. Individual user log-in access to this database will be granted to only those in the study team who require it for the performance of their role. Screening and recruitment logs of all patients approached to take part, and participants enrolled in the trial will be held at each site in secure password-protected files. Paper forms with participant-identifiable information will be held in secure, locked filing cabinets within a restricted area. Audio transcripts from the participant and staff interviews will be recorded on an encrypted device, with transcription completed by a member of the study team.

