#### Secondary outcome measures

Measures that will be used in the future full-scale trial will also be collected at baseline, 14 days or hospital discharge (whichever comes sooner) and at 30 and 90 days following randomisation. The proposed primary outcome for the definitive RCT will be days alive and out of hospital (DAOH) within 30 days. Out of hospital is classified as being at home or usual residence and defined as 30 minus the number of days in hospital (range 0–30), with 0 assigned for death within the 30 days. DAOH is a patient-centred outcome, has been validated with a range of clinical specialties^29^ and takes account of those patients who die or are discharged to community rehabilitation settings.

Further secondary outcomes include:

Physical function (30 s sit to stand test).Functional independence (Barthel Index).Quality of Life (EQ-5D-5L).

Additional outcomes collected are:

DAOH at 90 days.Hospital-acquired malnutrition (Global Leadership Initiative on Malnutrition - GLIM criteria).Weight and percentage change in weight.Time to complete therapy.Hospital discharge destination.Anthropometric measurements (mid-arm circumference, triceps skin fold, hand grip).

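### Data management ends collection at hospital discharge, against the 30- and 90-day schedule, and stops all data at withdrawal, so DAOH-30 is lost for anyone who withdraws before day 30

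*Protocol article*

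**What the plan says.** All of these are in the protocol article.

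- **Data management, end of collection:** "Data will be collected from the time the patient is considered for entry into the trial through to their discharge from hospital".
- **Data management, withdrawal:** for a participant who dies or withdraws, "identifiable data already collected with consent would be retained and used in the study". Then: "A withdrawal form will be completed, and no further data would be collected".
- **Data management, source:** "All data for an individual participant will be extracted from patient charts by the principal investigator or their delegated nominees".
- **Data collection:** clinical data are taken at baseline, daily in the intervention period, "and at 30 and 90 days post randomisation". Table 1 lists mortality and the resource-use questionnaire at both later times.
- **Secondary outcome measures:** DAOH within 30 days is the proposed primary outcome of the definitive trial, "defined as 30 minus the number of days in hospital (range 0–30), with 0 assigned for death within the 30 days". The additional outcomes include "DAOH at 90 days".
- **Data analysis, Table 2:** the retention criterion reads "Retention rates—defined as collection of primary outcome measure (days alive and out of hospital", with green only at 60 of 60 participants. The same section uses the DAOH-30 and DAOH-90 distributions to choose an analysis model and plan the definitive trial.

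**The concern.** DAOH-30 can be computed only if hospital days and vital status are known up to day 30, whenever the participant went home. A collection period that closes at discharge does not supply this, and one that closes at withdrawal does not either.

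The withdrawal rule matters more than usual here because retention is a primary outcome and Table 2 measures it by whether DAOH was collected. Each withdrawal before day 30 lowers a progression criterion and also removes a value from the data meant to plan the next trial. Some withdrawals are foreseeable. The intervention is daily and unblinded, and under Eligibility criteria those entered through a consultee are later asked whether they wish to continue, which gives both arms a second point of exit.

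Much of the loss may be avoidable. If data come from patient charts, hospital days and deaths could largely be obtained without any further contact, provided the participant agrees.

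**Working it through.** **1. Collection period, passages side by side.** Data management stops at discharge. Secondary outcome measures, Feasibility economic evaluation, Data collection and Table 1 all go to 90 days. Both cannot stand. Two illustrations, with days counted from randomisation, show what the discharge sentence would do if it were followed literally:

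- Discharged day 10, dies day 20: index stay alone gives 30 − 10 = 20; the definition gives 0.
- Discharged day 10, readmitted days 15 to 25: index stay alone gives 30 − 10 = 20; the definition gives about 30 − 10 − 10 = 10.

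If Table 1 prevails, the first case resolves, because mortality is recorded at 30 and 90 days. The second is less secure. Table 1 names post-ICU length of stay at the end of the intervention or discharge, but no readmission or hospital-day item afterwards. The resource-use questionnaire may cover hospital stays; the article does not say.

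**2. The plan's own retention figure.** Sample size gives 0.82 and 1 for a retention estimate of at least 40% per group of 30, at true rates of 50% and 80%. Exact binomial, true rate 50%: P(at least 13 of 30) = 0.819, which matches; the literal reading, P(at least 12 of 30), is 0.900. At 80% both are 1.000. This figure uses a different threshold from Table 2 and is not in dispute here.

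**3. Effect of the withdrawal rule on Table 2.** Inputs: n = 60 (Sample size); green = 60 of 60 and red = fewer than 36 (Table 2 participant counts). The article gives no withdrawal rate, so w, the share withdrawing before day 30, is assumed over a range. Withdrawals are taken as independent and as the only cause of a missing DAOH-30.

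- Cost of one withdrawal: 1/60 = 1.7 percentage points.
- Expected DAOH-30 values lost: 60w.
- P(green), rule as written: (1 − w)^60.
- P(green) if 80% of those withdrawing allow record follow-up (assumption): (1 − 0.2w)^60.

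| w | Lost, as written | P(green), as written | P(green), 80% permit |
|---|---|---|---|
| 2% | 1.2 | 0.98^60 = 0.30 | 0.996^60 = 0.79 |
| 5% | 3 | 0.95^60 = 0.046 | 0.99^60 = 0.55 |
| 10% | 6 | 0.90^60 = 0.002 | 0.98^60 = 0.30 |
| 20% | 12 | 0.80^60 < 0.001 | 0.96^60 = 0.09 |

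If every withdrawing participant gave permission, none would be lost through withdrawal.

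**4. Red boundary.** P(at least 36 of 60 collected), binomial with probability 1 − w, exceeds 0.999 for every w up to 20%. Table 2 also prints 50% beside this count; 50% of 60 would be 30, a still lower bar.

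**The case against.** The strongest reply is that the withdrawal sentence concerns leaving the study, and nothing says that declining physiotherapy, supplements or a visit counts as that. The Intervention section lets either component end early without saying that follow-up ends. Missed sessions and supplements are counted as fidelity data, which presumes those participants remain in. Telephone or video assessment is offered to those who cannot attend. The article also condenses a fuller protocol, and the contents of the withdrawal form and the consent supplement are not shown.

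Most of this stands. A reader might infer that anyone who stops the intervention loses all later data; the article does not say so. Nor can it be established that only one category of withdrawal exists. But the article does not merely leave the matter open: it states that collection ceases for a participant who withdraws, and mentions no continued follow-up by permission.

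Other limits also stand:

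- A reader might infer that deaths after discharge would be missed. That requires one sentence to override the whole follow-up schedule; the better reading is a contradiction to be reconciled.
- A reader might infer that loss would differ by arm and bias the DAOH mean and SD. Control participants can withdraw too, and no figure in the article shows the direction or size of any bias.
- Data already collected are kept, and withdrawal after day 30 costs DAOH-90 only.
- DAOH depends on the participant being back where they normally live, so hospital dates alone may not recover it fully.
- The steep fall in the probability of green comes largely from setting green at 100%.
- The objectives listed after the rationale define retention as completing the intervention; the dependence on DAOH holds for the Table 2 definition.

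**Conclusion.** The point holds in two parts. First, the article contradicts itself on when data collection ends, and the version in Data management cannot support DAOH-30 or DAOH-90. Secondly, the stated stop at withdrawal makes DAOH-30 unobtainable for anyone who withdraws before day 30, which lowers Table 2 retention by 1.7 points per person and makes green unlikely at quite ordinary withdrawal rates: about 0.30, 0.05 and 0.002 at 2%, 5% and 10%. Those rates are assumptions, and the calculation treats withdrawal as the only source of missing DAOH-30. Progression is not put in the red zone by this rule. Selective loss by arm remains a risk to guard against, not a demonstrated effect. The correction should be made because the loss is partly avoidable and affects the outcome the feasibility trial is meant to inform.

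**What to change.** 1. In Data management, change the collection period to run through 90 days after randomisation, and name hospital days, readmissions, place of residence and vital status among the data collected.
2. State that stopping the intervention or missing visits is not withdrawal from follow-up.
3. At withdrawal, seek permission for continued record follow-up of DAOH and mortality to day 90. End all collection only when the participant explicitly asks for that.

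The cost is an amendment to the withdrawal form and to the information and consent wording, with no extra visits. Records may not fully show whether a discharged participant is in their usual residence, so some DAOH values obtained this way may remain incomplete.
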